## 2. WORKING HYPOTHESIS AND PROPOSAL

We propose to use autologous transplantation of fecal microbiota to AML or HR MDS patients treated with intensive chemotherapy and antibiotics in order to restore the balance of their intestinal microbiome and thereby eradicate treatment-induced MDRB, infection-related complications, as well as sequelae to the gastrointestinal tract. Therefore, we propose to perform a single-arm multicentre prospective FMT trial in AML or HR MDS patients receiving intensive chemotherapy, and who are usually heavily treated with broad-spectrum antibiotics during aplasia that generate a profound status of dysbiosis. For this purpose, at the time of admission and diagnosis, patients will be requested to donate stools that will be comprehensively screened, and if deemed appropriate according to protocol criteria, conditioned and stored frozen until future processing and transplantation after aplasia completion.

## 3. OBJECTIVES

### ➤ Co-primary objectives:

- Efficacy of AFMT in dysbiosis correction in AML or HR MDS patients undergoing chemotherapy and antibiotherapy
- Efficacy of AFMT in MDRB eradication

### ➤ Secondary objectives:

- Definition of a dysbiosis biosignature

---

All documentation of **MaaT Pharma** is PROPRIETARY information and may not be forwarded to third parties without prior written consent from **MaaT Pharma**. Reproductions, either in part or in whole, may not be published or copied in any manner, without the explicit written consent of **MaaT Pharma**

|                                                                                   |                      |                                                                                               |
|-----------------------------------------------------------------------------------|----------------------|-----------------------------------------------------------------------------------------------|
| [figure not shown] | Protocol             | Protocol N°: MPOH02
EudraCT N° : 2015-004335-12
Version 10.0
Date : 20 November 2017 |
|                                                                                   | ODYSSEE STUDY |                                                                                               |

- Effect of dysbiosis correction on patient clinical status
- Short and mean term safety of AFMT in AML or HR MDS patients receiving intensive chemo- and antibiotherapy and receiving AFMT intervention during hospitalization
- Feasibility of the AFMT procedure and acceptability by the patient

#### **4. OUTCOME MEASUREMENTS**

##### **4.1. Efficacy of AFMT in dysbiosis correction**

Monitoring of microbiota deterioration following chemotherapy / antibiotherapy and dysbiosis correction after AFMT will be evaluated using indexes commonly used to characterize (Richness and diversity (such as Simpson or Shannon indexes) and between sample comparisons of the microbiota composition (Bray-Curtis distance, Sorensen, Pearson or Spearman indexes).

Microbiome diversity and richness will be measured at baseline, prior to the start of the induction chemotherapy, after induction chemotherapy/ antibiotherapy, post-AFMT and after consolidation chemotherapy/antibiotherapy. Metagenomic results of the 4 sequential samples will be compared in order to evaluate AFMT efficacy.

##### **4.2. Efficacy of AFMT in MDRB eradication**

Based on bacterial culture and analysis of resistance gene expression by metagenomics, we will evaluate the quantity of MDRB before, after chemotherapy/antibiotherapy and after AFMT.

##### **4.3. Definition of a dysbiosis biosignature**

A dysbiosis biosignature will be defined using association of:

- An innovative MaaT index based on microbial ecology (prevalence of pre-identified families / Genera / orders of bacteria ponderated by their beneficial or pathogenic effect on the host)
- Fecal and circulating inflammatory markers: calprotectin, neopterin, CRP
- Fecal marker of intestinal barrier integrity: zonulin

---

All documentation of **MaaT Pharma** is PROPRIETARY information and may not be forwarded to third parties without prior written consent from **MaaT Pharma**. Reproductions, either in part or in whole, may not be published or copied in any manner, without the explicit written consent of **MaaT Pharma**

|                                                                                                         |                      |                                                                                               |
|---------------------------------------------------------------------------------------------------------|----------------------|-----------------------------------------------------------------------------------------------|
| [figure not shown]
MaaT Pharma | Protocol             | Protocol N°: MPOH02
EudraCT N° : 2015-004335-12
Version 10.0
Date : 20 November 2017 |
|                                                                                                         | ODYSSEE STUDY |                                                                                               |

- Monitoring of blood immune cells
- Patient's clinical status (gastro-intestinal symptoms: nausea, vomiting, diarrhea, consistency and numbers of stools per day)
- Patient's quality of life

#### **4.4. Effect of dysbiosis correction on patient clinical status**

- Rate of *C. difficile* and other resistant bacteria until the hospitalization for consolidation chemotherapy
- Infectious-related mortality during 1 year post inclusion
- Infectious-related morbidity: fever, gastrointestinal tract events as diarrhea (severity and frequency), rates and recurrence, abdominal pain, bloating after AFMT and until 6 months after inclusion.
- Duration of hospitalization, duration, dose or change variations of systemic antibiotherapy after AFMT until 6 months after patient's inclusion
- Impact on early mortality and on chemosensitivity by measure of remission rate (partial or complete) until 1 year after patient's inclusion
- Impact on global survival and disease-free survival at 70 days, 6 months and 12 months after patient's inclusion

#### **4.5. Measurement of AFMT safety**

Tolerance of AFMT by monitoring safety during the transplantation period and until the next hospitalization: type and rate of adverse effects, with documentation on severity, relationship/imputability of adverse experience to AFMT. An adverse reaction is any unfavourable or unintended sign, symptom, or disease temporally associated with AFMT, whether or not considered linked to the procedure. A monitoring of adverse events (AE) and serious adverse events (SAE) will be performed during 12 months after patient's inclusion.

|                                                                                                         |                      |                                                                                               |
|---------------------------------------------------------------------------------------------------------|----------------------|-----------------------------------------------------------------------------------------------|
| [figure not shown]
MaaT Pharma | Protocol             | Protocol N°: MPOH02
EudraCT N° : 2015-004335-12
Version 10.0
Date : 20 November 2017 |
|                                                                                                         | ODYSSEE STUDY |                                                                                               |

#### **4.6. Measurement of AFMT feasibility and acceptability**

The AFMT feasibility and acceptability will be evaluated by the physician and the patient on a visual analogic scale (**Appendix 1**). Before and after chemotherapy clinical tolerance will be monitored in a logbook evaluating every day mood and quality of life, digestive symptoms (appetite, nausea, bloating, discomfort, pain), transit and stool characteristics using Bristol stool scale. The logbook will be given to the patient during study admission and carefully completed until the end of the study (**Appendix 2**). A health questionnaire EQ-5D-5L will be given to the patient at 4 timepoints (D0, D29, D40, and D70 see below) to evaluate more precisely the impact of AFMT on the quality of life.

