**Supplementary Table 9. Reasons for screening failure (n=37).**

|                                                          |                                                                                        |
|----------------------------------------------------------|----------------------------------------------------------------------------------------|
| Related to IMP manufacturing
n=22 (59%) | Insufficient raw material; n=14 (38%)                                                  |
|                                                          | Logistic failure; n=4 (11%)                                                            |
|                                                          | Quality control for batch release not reached; n=4 (11%)                               |
| Related to the patient
n=15 (41%)       | FMT not performed due to patients' condition; n=5 (14%)                                |
|                                                          | Patient's refusal to collection of the inoculum procedure (consent withdraw); n=3 (8%) |
|                                                          | AML diagnosis not confirmed; n=1 (3%)                                                  |
|                                                          | MDRB or C. difficile carriage at diagnosis; n=6 (16%)                           |

IMP: Investigational Medicinal Product; FMT: Fecal Microbiota Transfer; AML: Acute Myeloid Leukemia; MDRB: Multi-Drug Resistant Bacteria

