| TITLE                  | PreventiOn of DYsBioSis complications with autologous fecal microbiota transplantation in acutE myeloid leukemia patients undergoing intensive treatment: a feasibility and safety study (ODYSSEE STUDY)                                                                                                                                                                                                                                                                                                                                                                                                                                                                                                                                                                                                                                                                 |
| SPONSOR                | MaaT Pharma                                                                                                                                                                                                                                                                                                                                                                                                                                                                                                                                                                                                                                                                                                                                                                                                                                                       |

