#### **5.2. Exclusion criteria**

- Acute promyelocytic leukemia (AML-M3)
- Known allergy or intolerance to trehalose or maltodextrin
- Pregnancy: positive urinary or blood test in female of childbearing potential
- Severe disease with a life expectancy  $< 3$  months
- Other on-going interventional protocol that might interfere with the study
- Non eligibility for collection of autologous stools upon admission:
  - Patients refusing to consent
  - Antibiotherapy at the time of study inclusion  $\geq 4$  days
  - Concomitant or previous diagnosis of a significant inflammatory bowel disease (UC, CD) or other progressive digestive disease requesting treatment or further medical exploration

|                                                                                                         |                      |                                                                                               |
|---------------------------------------------------------------------------------------------------------|----------------------|-----------------------------------------------------------------------------------------------|
| [figure not shown]
MaaT Pharma | Protocol             | Protocol N°: MPOH02
EudraCT N° : 2015-004335-12
Version 10.0
Date : 20 November 2017 |
|                                                                                                         | ODYSSEE STUDY |                                                                                               |

- Presence of severe colitis of any etiology at the time of admission or severe digestive disorders (acute or chronic diarrhea) within 3 months preceding inclusion
- Presence of blood in faeces collected at the time of inclusion
- Patient getting a recent colonoscopy (within 3 months preceding inclusion)
- Detection of MDRB, pathogenic bacteria, parasites, norovirus and/or rotavirus during screening of autologous stool collected immediately after the inclusion visit
- Non eligibility for inoculum transplantation: persistent mucositis, colitis, or haemorrhoids, presence of blood in more than 1 patient's faeces out of 3 the week preceding the transplantation
- Non feasibility of inoculum procedure: patient refusal; technical or biological mismatch of the inoculum
- Absence of effective contraceptive method for female of childbearing potential
- Lactation
- Inability to give an informed consent

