### **6.2. Study duration**

Total duration of the study: 24 months

Inclusion period: Maximum 12 months (estimation)

The inclusion period will continue until the recruitment of 20 transplanted (AFMT) patients.

Participation period for a patient: Main period ≈ 70 days

Follow-up period: 1 year

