#### **6.4. Experimental plan and practical procedures**

This study aims to assess the feasibility and tolerance of AFMT in the setting of intensive chemotherapy delivered for the initial treatment of AML / HR MDS and the antibiotherapy given during aplasia

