| Evaluation de la faisabilité de la procédure de transplantation |
|------------------------------------------------------------------------|

A remplir par la personne ayant procédé à la transplantation

Entourer le chiffre correspondant

[figure not shown]

Très facile

Très difficile

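### Feasibility is measured only in patients who were transplanted, because failures to make or give the inoculum after enrolment are written as exclusions and replaced

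*Protocol*

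**What the plan says.** Feasibility is named in the study title, and protocol section 6.4 opens with it: "This study aims to assess the feasibility and tolerance of AFMT in the setting of intensive chemotherapy". Among the secondary objectives in section 3 it appears as "Feasibility of the AFMT procedure and acceptability by the patient".

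Section 4.6 gives the measure: "The AFMT feasibility and acceptability will be evaluated by the physician and the patient on a visual analogic scale". The rest of that section (logbook, EQ-5D-5L) concerns tolerance and quality of life. Appendix 1 contains the scale. The feasibility item runs from very easy to very difficult and is headed "A remplir par la personne ayant procédé à la transplantation". The patient items ask about comfort, pain and how the patient felt afterwards.

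Under section 6.4.2 the patient is enrolled at consent on Day 0. Stool screening, inoculum preparation and the decision to transplant around Day 30 all come later. Section 5.2 nevertheless lists among the exclusion criteria "Non feasibility of inoculum procedure: patient refusal; technical or biological mismatch of the inoculum", together with mucositis, colitis, haemorrhoids or blood in the stool shortly before transplantation. Section 6.2 sets the recruitment rule: "The inclusion period will continue until the recruitment of 20 transplanted (AFMT) patients". Section 6.3 and the synopsis give the study size simply as 20.

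**The concern.** For an autologous product made from stool collected at diagnosis, the practical question is what share of enrolled patients can have an inoculum made, released and given. The plan turns most of the ways this can fail into exclusions, replaces those patients, and measures feasibility only in those left. A failure of feasibility then removes the patient from the assessment of feasibility.

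This is not detail that a SAP would supply. The exclusion and replacement rules are protocol rules, and a rate calculated later would still meet them. At stake is how the result reads: favourable ease and comfort scores from the patients in whom the procedure went ahead would say nothing about the enrolled patients in whom it did not.

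**Working it through.** **Inputs.** Supplementary Table 9 lists 37 screening failures by reason. Supplementary Tables 2 to 6 report 25 treated patients. The protocol states no feasibility rate, target or denominator, so there is no planned figure to reproduce. The table can be checked against itself.

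**Check of Supplementary Table 9.**
- Manufacturing or logistics: 14 (insufficient raw material) + 4 (logistic failure) + 4 (batch release not reached) = 22; 22/37 = 59%.
- Patient-related: 5 (patient's condition) + 3 (refusal) + 1 (AML not confirmed) + 6 (MDRB or *C. difficile* carriage) = 15; 15/37 = 41%.
- Total 22 + 15 = 37. All printed percentages agree after rounding.

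Failures to make or give the product number 22 + 5 + 3 = 30 of the 37. The other 7 are carriage and the unconfirmed diagnosis.

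**Receipt of AFMT.** Assumption: the 25 treated and the 37 failures are all the patients enrolled, so N = 25 + 37 = 62. The documents do not state total enrolment. Intervals are Clopper-Pearson: the lower limit is the 0.025 quantile of Beta(x, n − x + 1) and the upper limit is the 0.975 quantile of Beta(x + 1, n − x).

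| Denominator | x/n | Proportion | Exact 95% CI |
|---|---|---|---|
| All enrolled (assumed) | 25/62 | 40% | 28% to 54% |
| Without carriage and unconfirmed AML (62 − 6 − 1) | 25/55 | 45% | 32% to 59% |
| Also without refusals (55 − 3) | 25/52 | 48% | 34% to 62% |
| Treated plus the 22 manufacturing or logistic failures only | 25/47 | 53% | 38% to 68% |
| Transplanted only, as the protocol's rules imply | 25/25 | 100% | by construction |

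Supplementary Table 3 has blood pressure values for all 25 at both the first and the second AFMT. In these data, receipt of one and receipt of both therefore appear to coincide.

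**Enrolment needed for 20 transplanted.** At 25/62 this is 20 × 62/25 = 49.6, so 50 patients. At 25/55 it is 44, and at 25/47 it is 37.6, so 38. Section 6.3 gives 20 and does not separate included from transplanted patients.

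**The case against.** The strongest reply concerns scope. The secondary objective speaks of the feasibility of the AFMT procedure, and an operator's ease rating is a fair measure of that. The co-primary objectives are about efficacy. This has force: the scale fits the narrow objective and should stay. The title and section 6.4 use feasibility more broadly, however, and section 5.2 itself applies the term non-feasibility to refusal and inoculum mismatch.

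Second, the unseen SAP may define delivery proportions over all included patients. It may, so the absence of a rate is not the point. The point is that the measure, exclusions and replacement rule fixed in the protocol all work against one.

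Third, a reader might infer more than the documents support:
- *That feasibility cannot be answered at all.* The failures were kept and tabulated by reason, so a rate near 40% can be calculated afterwards. The planned measure does not provide it.
- *That full delivery is 100% by construction.* Only receipt of at least one AFMT is. Section 6.4.2 lets the second AFMT be withheld after certain events, and Appendix 1 records incomplete injection, expulsion and volume lost.
- *That feasibility rests on a comfort score.* The feasibility item is the operator's rating of ease. Comfort and pain are separate patient items. The protocol has no rule for declaring AFMT feasible.
- *That every screening failure is a feasibility failure.* Pathogen detection is an openly stated eligibility step, and an unconfirmed diagnosis has nothing to do with the product. Both need separate display.
- *That the efficacy comparison is invalidated.* It is a paired before-and-after contrast that needs treated patients, and the transplanted-only target is stated openly.

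**Conclusion.** The point stands as a design weakness on a declared aim. The only stated feasibility measure exists solely for transplanted patients, while failures after enrolment to make or give AFMT are labelled exclusions and replaced. The measure therefore addresses ease and acceptability and leaves open whether AFMT can be made and delivered in enrolled patients.

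The effect is large on any denominator tried: 40% received AFMT (28% to 54%) if all 62 count, and up to 53% (38% to 68%) if only manufacturing and logistic failures count against it, compared with 100% in the population the rules leave. These figures rest on the assumption that the treated patients and screening failures together are everyone enrolled. The structural point does not depend on it.

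**What to change.** - **Section 4.6:** define feasibility as the proportions of all patients enrolled at Visit 1 who had an inoculum manufactured, released, given once, given twice and fully injected. Report each with a Clopper-Pearson interval, and add a table of reasons for not reaching each step.
- **Carriage and diagnosis:** show pathogen-positive screening and unconfirmed diagnosis as separate rows, with a sensitivity denominator that leaves them out.
- **Visual scale:** keep it, as the measure of ease and acceptability among transplanted patients.
- **Section 5.2:** relabel the conditions that arise after enrolment as reasons for not transplanting, and keep those patients in the enrolled set. Who is transplanted does not change.
- **Sections 6.2 and 6.3:** state the enrolled and the transplanted numbers separately.

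The cost is wording and one table, from data already collected. The downside for the sponsor is that the reported feasibility becomes less favourable.

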### **5. SELECTION OF POPULATION FOR THE STUDY**

#### **5.1. Inclusion criteria**

- Patients  $\geq 18$  and  $\leq 75$  years old with *de novo* diagnosis of AML or HR MDS for whom intensive induction chemotherapy is anticipated within 10 days after admission Patients willing to donate stool samples and to follow protocol recommendations
- Signature of informed and written consent

#### **5.2. Exclusion criteria**

- Acute promyelocytic leukemia (AML-M3)
- Known allergy or intolerance to trehalose or maltodextrin
- Pregnancy: positive urinary or blood test in female of childbearing potential
- Severe disease with a life expectancy  $< 3$  months
- Other on-going interventional protocol that might interfere with the study
- Non eligibility for collection of autologous stools upon admission:
  - Patients refusing to consent
  - Antibiotherapy at the time of study inclusion  $\geq 4$  days
  - Concomitant or previous diagnosis of a significant inflammatory bowel disease (UC, CD) or other progressive digestive disease requesting treatment or further medical exploration

|                                                                                                         |                      |                                                                                               |
|---------------------------------------------------------------------------------------------------------|----------------------|-----------------------------------------------------------------------------------------------|
| [figure not shown]
MaaT Pharma | Protocol             | Protocol N°: MPOH02
EudraCT N° : 2015-004335-12
Version 10.0
Date : 20 November 2017 |
|                                                                                                         | ODYSSEE STUDY |                                                                                               |

- Presence of severe colitis of any etiology at the time of admission or severe digestive disorders (acute or chronic diarrhea) within 3 months preceding inclusion
- Presence of blood in faeces collected at the time of inclusion
- Patient getting a recent colonoscopy (within 3 months preceding inclusion)
- Detection of MDRB, pathogenic bacteria, parasites, norovirus and/or rotavirus during screening of autologous stool collected immediately after the inclusion visit
- Non eligibility for inoculum transplantation: persistent mucositis, colitis, or haemorrhoids, presence of blood in more than 1 patient's faeces out of 3 the week preceding the transplantation
- Non feasibility of inoculum procedure: patient refusal; technical or biological mismatch of the inoculum
- Absence of effective contraceptive method for female of childbearing potential
- Lactation
- Inability to give an informed consent

